## Statistical analysis of results

Statistical analysis will involve the calculation of mean, standard deviation, minimum and maximum values for the descriptive analysis of the effects of tDCS and VR on the quantitative variables. The Shapiro-Wilk normality test will be used to determine the distribution of the data in terms of adherence to the Gaussian curve. Parametric variables will be expressed as mean and standard deviation. Nonparametric variables will be expressed as median and interquartile range.

For phase 1, either Student’s *t*-test or Mann-Whitney test will be used to compare quantitative variables between the TD and DS groups. In phase 2, descriptive measures of mean and standard deviation will be used as initial values for the calculation of the sample size in phase 3. In phase 3, we will analyze quantitative variables with measures over time (pre-intervention, post-intervention and one-month follow-up) and comparisons of the EG and CG will be performed using repeated-measures ANOVA. The level of significance will be set at 5% for all statistical tests. The data will be organized, tabulated and analyzed with the aid of the Statistical Package for the Social Sciences (v.25.0).

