### Sample size

A convenience sample will be used in phase 1, which will be an exploratory analysis to identify and compare the profile and motor variables of children with DS and TD. Phase 2 will be a pilot study with a random, exploratory sample using the formula of Student’s *t*-test with a minimum power of 80% (power equal to type II error) and 5% significance level (power equal to type I error) to furnish the calculation of the sample size for phase 3. Phase 3 will be a randomized controlled clinical trial with the sample size based on the findings of phase 2.

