### Group allocation

The allocation of the participants will be concealed in sequentially numbered, sealed, opaque envelopes prepared prior to the study by a research assistant who will not be involved in the study. After the baseline measures have been collected, participants will be randomly assigned to the experimental or control group by the treating therapist, who will open the envelopes and read the contents. All outcomes will be measured by blinded assessors. All enrolled participants will receive a code to protect confidentiality before, during, and after the trial.

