### Recruitment

Strategies will be employed to encourage participation in the study and reduce the dropout rate. The children with DS will be recruited from the outpatient clinic of the University Center of Anápolis and the Association of Parents and Friends of Exceptional Children of Anápolis. Parents/guardians will be contacted by telephone (or other means of communication). Pamphlets will be created with a brief description of the objectives, type of therapeutic intervention, expected results and eligible population. The researchers of the project will be responsible for this disclosure as well as leaving contact information for the parents of eligible children. The children selected for this study will be recruited according to the schedule registered with the ethics committee and REBEC in December 2020.

#### Study 1

A cross-sectional study will be conducted to determine the pattern of normality in children with typical development and compare the pattern to that found in children with DS. The sample selected for this study will be in accordance with the eligibility and quantity criteria for a convenience sample. The participants will be divided into two groups and each group will consist of 12 children.

#### Study 2

A pilot study will be conducted to determine the sample size for the randomized controlled clinical trial. For the proper sample size calculation, the pilot study will be carried out using the same methods as those to be employed in the main study and will involve ten children selected based on the eligibility criteria for the children with DS. The sample size for the clinical trial will be calculated based on the means obtained in the experimental and control groups of this pilot study, considering brain activity as the primary outcome, a unidirectional alpha of 0.05 and a power of 80%. The sample size will be then increased by 20% to compensate for possible dropouts.

#### Study 3

A randomized controlled trial will be conducted. The sample will be selected based on the results of the pilot study and the children will be randomly distributed into two groups using a randomization website (www.random.org).

The experimental group is as follows: anodal tDCS (anode placed over F3 of the International 10-20 Electroencephalogram System and cathode placed over right deltoid muscle) combined with VR training.

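### Phase 3 treats the pre-randomisation baseline as an outcome level in a repeated-measures ANOVA and is to be sized by a one-sided t-test: valid, but inefficient and mismatched

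*Protocol article*

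**What the plan says.** **Analysis.** Under Statistical analysis of results, the phase 3 variables are described as having "measures over time (pre-intervention, post-intervention and one-month follow-up". The test of active against sham is then named: "comparisons of the EG and CG will be performed using repeated-measures ANOVA". The article names neither the ANOVA effect (group or group-by-time) that tests the hypothesis nor a baseline covariate. The significance level is 5% for every test, and the software is SPSS v25.

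**Baseline.** Group allocation states: "After the baseline measures have been collected, participants will be randomly assigned to the experimental or control group". Any baseline difference between arms is therefore due to chance.

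**Sizing.** Under Sample size: "Phase 2 will be a pilot study with a random, exploratory sample using the formula of Student’s *t*-test", with 80% power and 5% significance. In the Study 2 paragraph under Recruitment, the source of the phase 3 effect is given: "calculated based on the means obtained in the experimental and control groups of this pilot study". The outcome, direction and target power for that calculation are also fixed there: "considering brain activity as the primary outcome, a unidirectional alpha of 0.05 and a power of 80" per cent. An allowance for losses follows: "The sample size will be then increased by 20% to compensate for possible dropouts". The statistical section adds that "descriptive measures of mean and standard deviation will be used as initial values for the calculation of the sample size in phase 3".

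**Hypothesis.** Under Objective/hypotheses, the alternative is that active and sham results differ, with no direction given.

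**The concern.** Treatment cannot affect a value measured before allocation. When that value enters as an outcome level, the group main effect averages a visit with zero expected difference together with the two visits that matter; if the effect is sustained, it recovers only two thirds of it. The group-by-time test avoids this dilution, but it spreads its power over two degrees of freedom and does not by itself give one active-minus-sham difference.

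The t-test that sets the size is neither of these. It compares two means at one unspecified time, in one direction, while the ANOVA F test has no direction. The number of children is therefore planned for a question that the analysis does not ask. In a small trial, where measurements are costly to obtain, the power delivered can fall well short of the 80% intended.

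**Working it through.** **Inputs from the article:** 1:1 allocation, three visits, baseline before randomisation, one-sided 0.05 and 80% power for sizing, plus 20% for dropouts, 5% for all tests. There is no phase 3 figure to reproduce, because the size awaits the pilot.

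**Assumptions:** standardised effect d = 0.7 at both later visits, equal variances, the same correlation ρ between all visits, and tests at two-sided 5%. With d = 0.7 the article's own sizing rule gives n = 26 per arm (one-sided t-test power 80.1% at 26, 78.7% at 25), before the 20% increase.

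**Noncentrality λ** (power from the noncentral F), with n·d² = 26 × 0.49 = 12.74:
- Baseline-adjusted post value: λ = n·d²/[2(1−ρ²)], df 1 and 2n−3
- Group-by-time: λ = n·d²/[3(1−ρ)], df 2 and 4n−4
- Group main effect: the mean difference over three visits is 2d/3 and the variance of a child's mean is (1+2ρ)/3, so λ = (2/3)n·d²/(1+2ρ), df 1 and 2n−2
- Baseline-adjusted mean of the two later visits: λ = n·d²/{2[(1+ρ)/2−ρ²]}, df 1 and 2n−3

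At ρ = 0.5:
- adjusted post: 12.74/1.5 = 8.49
- group-by-time: 12.74/1.5 = 8.49, but on 2 df
- group main effect: 8.49/2 = 4.25
- adjusted mean: 12.74/1 = 12.74

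| ρ | Adjusted post | Group-by-time | Group main effect | Adjusted mean |
|---|---|---|---|---|
| 0.2 | 71% | 52% | 68% | 91% |
| 0.3 | 74% | 58% | 62% | 91% |
| 0.5 | 82% | 73% | 52% | 94% |
| 0.7 | 93% | 92% | 45% | 98% |
| 0.8 | 98.5% | 98.7% | 43% | 99.8% |

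Solving the same formulas for 80% power at ρ = 0.5 gives 26 per arm for adjusted post, 31 for group-by-time and 50 for the group main effect.

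**Sidedness alone.** At 26 per arm the t-test on post values has λ = 12.74/2 = 6.37. Its power is 80% one-sided and 70% two-sided.

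**Other time courses** (n = 26, ρ = 0.5). For group-by-time, λ = (n/2)·Σ(δ−mean δ)²/(1−ρ), where δ is the effect at each of the three visits.
- Growing effect (0.35 SD post, 0.7 SD at one month): adjusted post λ = 26 × 0.1225/1.5 = 2.12, power 30%; group-by-time λ = 13 × 0.245/0.5 = 6.37, power 60%; adjusted mean λ = 26 × 0.525² = 7.17, power 75%.
- Fading effect (0.7, then 0.35): adjusted post 82%, group-by-time 60%, adjusted mean 75%.

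**Cross-check with d = 0.8.** The sizing rule gives 21 per arm. At ρ = 0.5, power is 83% (adjusted post), 75% (group-by-time), 54% (group main effect) and 95% (adjusted mean). If the effect is present at post only, the adjusted mean falls to 43%, against 75% for group-by-time and 83% for adjusted post.

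**The case against.** **The planned test is a standard one.** Group-by-time in a repeated-measures ANOVA validly tests whether change differs between arms. That stands: the point is efficiency and matching, not validity.

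**The loss is conditional.** It depends on a correlation that the article does not give and on an ANOVA effect that it does not name. That stands too. At correlation 0.7 or more, group-by-time is about as powerful as the adjusted post comparison. The largest losses apply only if the group main effect is the test.

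**The mismatch in sizing runs both ways.** At correlation 0.5, group-by-time (73%) has slightly more power than a two-sided t-test on post values (70%). The t-test's own fall from 80% to 70% comes from sidedness, not from the ANOVA. This stands, and is why the sizing must match in both contrast and sidedness. Study design does expect superiority of the active arm, which could support a one-sided test, but the stated alternative and the F test have no direction.

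**A post-intervention contrast may not be the better choice.** The Discussion cites an earlier study of the same combination whose clearest alpha findings came one month after treatment. With a growing effect, the adjusted post contrast has 30% power against 60% for group-by-time. This stands and shapes the fix.

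**A reader might infer that only complete cases will be analysed.** The article does not say so. It states no missing-data rule and names no SPSS procedure, and such detail is commonly left to the full protocol or analysis plan. Only the classical form of the ANOVA drops a child who misses one visit. Even then the planned increase offsets much of the loss: 26 × 1.2 ≈ 31 per arm, of whom 80%, about 25, are complete, giving group-by-time about 71% power at correlation 0.5 (λ = 25 × 0.49/1.5 = 8.17).

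**Conclusion.** The point holds as one of inefficiency and mismatch, and is worth changing before phase 3 is sized. Under the assumed values (26 per arm, 0.7 SD at both later visits, correlation 0.5), the planned model gives up about 9 points of power if group-by-time is the test (82% against 73%) and about 30 points if the group main effect is (82% against 52%). Against group-by-time the loss is about 16 points at correlation 0.3 and close to nil from 0.7. For the group main effect a loss appears at every correlation tried, from about 3 points at 0.2 to 48 points at 0.7.

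These figures rest on equal correlations between visits, equal variances and a sustained effect, none of which the article gives. Two stronger conclusions are not supported: that the ANOVA is an invalid test, and that a wrong sample size has already been computed, since the calculation is still to follow the pilot.

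**What to change.** In Statistical analysis of results, replace the phase 3 sentence with a linear mixed model, which the same software fits, for the post-intervention and one-month values. Terms: group, visit, group-by-visit, and the baseline value as covariate. Include all randomised children with any post-baseline value.

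Before the data are seen, name one primary active-minus-sham contrast, reported with a 95% confidence interval. This would be the post-intervention difference, or the average of the two later visits if a delayed effect is thought plausible, as the Discussion suggests.

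In Sample size and in the Study 2 paragraph, base the phase 3 calculation on that same contrast and the same sidedness.

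Cost: wording only, with no added visits or measurements. Because phase 3 is not yet sized, the sample-size text can change at the same time; the number of children will then follow from the chosen contrast and sidedness. The small downside is that a single named contrast can lose power if the effect follows a different time course, as the growing-effect and post-only cases show.

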## Discussion

Neurological disorders in children with DS can lead to deficits in perceptual interactions as well as a poorer functional performance [10] compared to children without this syndrome [21–25]. Delays in the acquisition of basic motor skills are common in this population, indicating that such skills emerge at a different time compared to children with typical development [12, 21, 22].

VR activities constitute a promising resource in the rehabilitation process by promoting the repetition of movements during functional and motor training, the improvement of sensorimotor and adaptive information, and the overcoming of difficulties with regards to activities of daily living [50, 51]. Moreover, tDCS provides the possibility of optimizing the effects of motor training through a VR game by modulating cortical excitability. According to the literature, the combination of these two techniques is appropriate for this population.

The optimization of the results obtained through VR games is believed to be related to interactive training with a wide range of activities and scenarios involving multiple sensory channels and the creation of exercises, the intensity of which can be adjusted to the needs of children with DS [51–53]. Thus, this study is expected to provide evidence that supports findings reported in the literature. Lopes et al. suggested that tDCS combined with a VR game for children with DS may influence brain activity by acting on local circuits [54, 55]. In another study involving tDCS combined with VR, Miziara et al. found better alpha events in the somatosensory region, especially at the assessment performed 1 month after the end of the intervention. Moreover, greater alpha desynchronization was found after stimulation plus training, indicating an increase in attention and concentration during the preparation of movements. To achieve better results, the authors state that it is necessary to conduct a study with a larger sample, as VR may influence the EEG signal [56–58]. Therefore, the proposed study aims to complement the literature with further information and different variables to provide the scientific community with clinical data on this combination of interventions.

## Data Availability

The methods of disseminating the original data will be reported according to the research process and the results of the study will be presented in peer-reviewed journals. The full protocol will be made available. Data cannot be shared publicly because this study has been approved by the research ethics committee, which requires that study data (including unidentified data) be released only after completion.

## Abbreviations

CAPES: *Coordenação de Aperfeiçoamento de Pessoal de Nível Superior*
CNPq: *Conselho Nacional de Desenvolvimento Científico e Tecnológico (Brazilian National Council for Scientific and Technological Development (CNPq))*
CONSORT: Consolidated Standards Of Reporting Trials
DLPFC: Dorsolateral Prefrontal Cortex
DS: Down Syndrome
EEG: Electroencephalography
EMG: Electromyography
MEG: Magnetoencephalography
REBEC: Brazilian Registry Of Clinical Trials
SPIRIT: Standard Protocol Items: Recommendations for Interventional Trials
TD: Typical Development
tDCS: Transcranial Direct Current Stimulation
VR: Virtual Reality
WASI: Wechsler Abbreviated Scale of Intelligence
WASI II: Wechsler Intelligence Scale for Children
